| Statistical analysis | 1. General principles  Analyses will be descriptive in nature. Descriptive analyses will include the number of observations, mean, standard deviation, median, range, and interquartile range for continuous variables and the number and percent for categorical variables.  2. Populations  - ITT(Intent-to-Treatment): Defined as all assigned patients. However, patients who did not take the investigational product at least once in the ITT group should be excluded from the analysis group.  - PP(Per Protocol): PP analyses exclude all protocol major violation, including anyone who did not adhere to treatment, switched groups, or missed measurements.  - The final evaluation will be based on the results of the ITT group analysis.  3. Safety analysis  After agreeing to participate in the study, the study will be defined as the whole box of randomized, at least one investigational product.  4. Primary efficacy variable analyses  In the baseline, 3 months after the administration of CIN I, the patient was judged to be cured to normal, and the response rate between the PGA group and the control group was compared.  The evaluation of the healing rate between the groups is based on the method proposed by Jung (2008). When the results were confirmed by selecting 43 patients in each group, as in the previous step, the difference in the number of patients. In the case of less than 2 persons (PGA group-Control group), it was judged that there is no effect of PGA, and the present study is terminated. If there are more than 2 difference in level 1, 37 patients per group are recruited. In case of more than +11 patients who were judged as Histologic resolution by 80 patients per group, Histologic resolution of CIN. It is judged that there is an effect of PGA. If there is less than +11, it is concluded that the effect of PGA is not ultimately.  5. Secondary efficacy variable analyses  Secondary efficacy variable 1: Reid Colposcopic Index  0-2 Score: Likely to be CIN I  3-4 Score: Overlapping lesion - likely to be CIN I or CIN II  5-8 Score: Likely to be CIN II  The comparison between the baseline scores and the difference of the scores after 12 weeks will be confirmed through the t-test or the Wilcoxon rank sum test. In addition, considering the multinomial distribution of the grading system (0-2, 3-4, 5-8 points), the cumulative or ordinal logistic model of the changes in the grading system after 12 weeks compared to baseline.  Secondary efficacy variable 2: Pap Smear Test  The reading standard is based **on the 2001 Bethesda System for Reporting Cervical Cytologic Diagnoses**. The results of the study were divided into 6 stages: Negative, ASC-US, ASC-H, LSIL, HSIL, and Invasive cancer (Cervical carcinoma). Considering the multinomial distribution, And the cumulative or ordinal logistic model is used to analyze changes in the classification stage 3 months after the baseline.  Secondary efficacy variable 3: HPV DNA Chip Test  The HPV DNA Chip Test is a test to determine the type of virus infection. It is classified as positive or negative according to the test result. GEE (Generalized Estimating Equation) or Generalized Linear Mixed Model is considered to determine time-dependent changes, group-to-group differences, and time-to-group interactions for baseline versus measured clearance.  Secondary efficacy variable 4: HPV HC Ⅱ assay  GEE (Generalized Estimating Equation) or Generalized Linear Mixed Model is considered to determine time-dependent changes, group-to-group differences, and time-to-group interactions for baseline versus measured clearance.  Secondary efficacy variable 5: NK cell activity  To compare the results of NK cell activity measured at 4 weeks, 8 weeks, and 12 weeks versus baseline (0 week), the mean difference between the baseline and 12-week NK cell levels was calculated as t - Black or Wilcoxon rank sum test.  Secondary efficacy variable 6: MHC class II CD8, CD56 population  GEE (Generalized Estimating Equation) or Generalized Linear Mixed Model is considered to determine time-dependent changes, group-to-group differences, and time-to-group interactions for baseline versus measured clearance.  6. Safety analyses  All safety data, including all adverse events collected from patients, clinical laboratory test results, 12-lead ECG, and vital signs (blood pressure and pulse rate) are performed.  1) Adverse events  Summarize the adverse events observed following administration of the investigational product. The number of cases and the number of patients who experienced an adverse reaction, abnormal drug response, SAE, death, adverse events n that caused discontinuation of clinical trial, and / or "other significant adverse events (OAE) do. The number of patients who received each of the abnormal responses was also summarized by body-organ system (SOC), recommended language, and maximum severity for each treatment group. In addition to the summary statistics, the incidence or incidence of adverse events in the group are analyzed using Chi-squared test, Fisher's Exact test, or Poisson test.  2) Vital signs and laboratory tests  The results were analyzed by Chi-squared test, Fisher's Exact test, or Poisson test for each group of 12-lead ECG abnormalities at each time point. A summary statistic is presented and, if necessary, GLM or GLMM methods are used to perform group comparisons. |

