### 9.3 Sample size

#### 9.3.1 Sample size

##### - Total 200 patients (PGA Group 100 patients, Placebo Group 100patients)

Based on published literature, we assumed that 31% of the cases of CIN 1 would resolve spontaneously, and a clinically significant difference was estimated at 20%. 80 patients per group.

| Group | Dose | Patient | Expected response Rate | Expected response patient | Duration of treatment/Observation |
| --- | --- | --- | --- | --- | --- |
| Placebo | - | 80 | 31% | 24.8 | administered once daily for 4 weeks /  observation for 8 weeks |
| PGA | 1,500mg/day | 80 | 51% | 40.8 |  |
| Total | - | 160 |  |  |  |

Cervical intraepithelial neoplasia (CIN I) can act as a precursor to invasive cervical cancer and is the most common significant gynecologic disease in women of reproductive age. study, we investigated clinical efficacy and immune response of oral administration of γ-PGA from women with cervical intraepithelial neoplasia 1 (CIN 1) in phase 2b study

H_0_ : p_1_≦p2 vs. H_1_ : p_1_>p_2_

p_1_ : Response rate of treatment, p_2_: Response rate of Control

Expected response rate: PGA Group: 81%, Control Group: 51%

significance level : 0.05, statistical power : 80%, one-sided test

The Sample size is total 160 patients, 80 patients per group when the Single stage method.

If 20% drop out is considered, the sample is total 200 patients, 100 patients per group

The sample size is according to the Two stage optimal design (Jung(2008)) Method is shown in the following table.

[Jung(2008) Two-stage]

| Stage | Patient | Difference between two groups (Treatment patient-Control patient) | 제 significance level, statistical power |
| --- | --- | --- | --- |
| 1  2 | 43  80(43+37) | +2  +11 | 0.461, 0.800 |

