###### 9.3.2 Basis of calculation

The prevalence of Cervical intraepithelial neoplasia (CIN I) in the Korean population is very limited, and there is little clinical study on the efficacy of the treatment [6]. In this study, To investigate the effect of glutamic acid, we refer to the results of research abroad.

Most of the studies on natural cure rates for Cervical intraepithelial neoplasia (CIN I) were done for more than 6 months. The natural cure rates at 3 months as in the present study were compared with those of CIN I and II (Barnett et al. As a result of the study, about 31% in the placebo group and about 33% in the photodynamic therapy (PDT).[8] A 15-week study of Trimble (2005) with CIN II and III showed a natural cure rate of 28%. [9]

In a study by Bansal et al. (2008), who conducted a cohort study, the study included 1001 CIN I patients who were followed up for at least 12 months to determine the natural cure rate at the 6-month follow-up, approximately 49% of the patients were reported to return to normal. [10]

In a phase 2 clinical trial (Hefler et al., 2010) to confirm the effect of topical infusion of progesterone in a similar clinical trial phase, the natural cure rate of the control group without special treatment was 38.8% of 96 patients. [11]

Based on the results of the above studies, it can be summarized that most of the natural cure rates are within 3 months and the additional effect after 3 months is about 7.8% ~ 18.0%. The natural cure rate at 3 months was set at 31.0%.

This study was established as an exploratory study with phase 2 clinical studies and it was concluded that at least 20% of the effects of high natural healing rates should be clarified to enable large scale clinical studies. Was not worth it.

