**[11] Study Methodology**

The purpose of this study was to investigate the effect of oral administration of poly-gamma glutamic acid (γ-PGA) on the Cervical Intraepithelial Neoplasia (CIN I) Double-blind, placebo-controlled study designed to identify immunomodulatory effects by assessing changes in immunological parameters.

In this study, a total of 80 patients (100 patients in the case of dropout) were participated in the study. Participation in the study was conducted in two stages as proposed by Jung (2008). In the first stage, 43 subjects were recruited in each group, and the main effect variable, healing, was checked. The difference in the number of subjects in the clinical trial for healing was less than 2 (the number of subjects who were treated for healing of poly-gamma glutamic acid - The number of subjects in clinical trials), it is judged that there is no effect of poly-gamma glutamic acid on cervical epithelial dysplasia and the study is terminated.

If there is more than one difference in step 1, we will consider a two-step study design that will enter step 2 and add an additional 37 patients per group. If the difference in the number of subjects in the clinical trial between group 1 and group 2 of 80 patients in each group is greater than 11 patients, the effect of γ-PGA will be confirmed. Otherwise, γ-PGA. It will be judged that it is not effective in healing the injured Cervical Intraepithelial Neoplasia (CIN I).

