#### 15.3.4 Analysis of primary efficacy endpoints

In this study, the primary efficacy endpoint was to determine the cure rate as normal at the third month of drug administration of CIN I at baseline as described in 15.2.1 and compare the healing rates between the test and control groups.

The evaluation of the healing rate between the groups was based on the method proposed by Jung (2008). As described above, when 43 patients were selected in each group (intermediate analysis) in the first step, When the difference in number is less than 2 (test group-control group), it is judged that there is no effect of poly gamma glutamic acid, and the present study is terminated. If there were two or more difference in level 1, 37 patients were recruited in each group. In the case of more than 11 patients who were judged to be cured by 80 patients per group, it is judged that there is an effect of poly gamma glutamic acid. If it is less than 11, it is concluded that the effect of poly-gamma-glutamic acid is not ultimately.

If the final number of subjects is different in each analysis group after the end of step 2.

[figure not shown]

here,

n1, n2: Number of subjects per group in steps 1 and 2

a1, a: The first and final stages to determine whether to adopt the null hypothesis. The difference between the groups of healed subjects y1, y2, x1, x2:

b (y|n, p): probability distribution of binomial distribution

We will present the p-value based on the significance level formula.

In addition, the number of children, number of sex partners, and whether smokers are covariates during baseline diagnosis will be analyzed by logistic regression analysis using "exploratory analysis"

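### Missing a one-sided superiority boundary is written up as a finding that PGA has no effect, although final differences of 5 to 10 cures do not exclude the protocol's own 20-point target

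*Protocol*

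**What the plan says.** Section 9.3.1 sets up a superiority test only: the null hypothesis is that the PGA response rate does not exceed the control rate, with "significance level : 0.05, statistical power : 80%, one-sided test". On the size of effect it states that "we assumed that 31% of the cases of CIN 1 would resolve spontaneously, and a clinically significant difference was estimated at 20" per cent. The two-stage table gives 43 and then 80 patients per group, with boundaries of +2 and +11.

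Three places then attach a conclusion to a missed boundary:

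- **Section 15.3.4**, final analysis: "If it is less than 11, it is concluded that the effect of poly-gamma-glutamic acid is not ultimately". Below 2 at stage 1, the same section judges PGA to have no effect and ends the study.
- **Section 11**, stage 1: "it is judged that there is no effect of poly-gamma glutamic acid on cervical epithelial dysplasia and the study is terminated". At the end, anything not above 11 is judged not effective.
- **Protocol Outline**, primary efficacy analysis, stage 1: "it was judged that there is no effect of PGA, and the present study is terminated". Its wording at +11 matches Section 15.3.4.

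Section 9.3.2 describes a narrower purpose. The study is exploratory, and "at least 20% of the effects of high natural healing rates should be clarified to enable large scale clinical studies". Section 15.3.1 provides a 95% confidence interval where one is needed. Section 15.3.4 promises a p-value. Neither enters the stated conclusion.

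**The concern.** A one-sided superiority test has two outcomes: superiority shown, or superiority not shown. To conclude that a product does nothing, or nothing worthwhile, one needs a margin and an interval whose upper limit lies below it. The protocol sets no such margin, yet prescribes the negative conclusion in all three places.

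What is at stake is what a failed trial may say. Section 9.3.2 asks whether a large study is justified, and a missed boundary answers that. It does not answer whether PGA has an effect. A result just short of +11 would be labelled no effect while remaining compatible with the difference that the protocol itself calls clinically significant.

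**Working it through.** **Inputs.** From Section 9.3.1: placebo 31%, PGA 51%, 43 then 80 per group, boundaries +2 and +11, one-sided 5%. Placebo cures are taken at the assumed rate: 0.31 × 80 = 24.8, rounded to 25; 0.31 × 43 = 13.3, rounded to 13.

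**Step 1: reproduce the design.** Let D1 be the difference in cures with 43 per group and D the difference with 80 per group. The probability of success is P(D1 ≥ 2 and D ≥ 11), from exact binomial probabilities.

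- At 51% against 31% it is 0.805; the table prints 0.800.
- With equal rates it is 0.0461 at 50% and 0.035 at 31%. The printed significance level of 0.461 looks like 0.0461 with a zero lost.
- Section 9.3.1 also prints "Expected response rate: PGA Group: 81%, Control Group: 51" per cent. That pair would give a power of 0.989, so 51% against 31% is the design basis.

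The boundaries therefore work as a one-sided 5% superiority rule. A fixed-sample check agrees. For D = 10 the pooled rate is 60/160 = 0.375, z = 0.125 / √(2 × 0.375 × 0.625 / 80) = 1.63, one-sided p = 0.051. For D = 11, p = 0.037.

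**Step 2: intervals at the final analysis.** With p1 = (25 + D)/80 and p2 = 25/80, the Wald interval is (p1 − p2) ± z × SE, where SE = √[p1(1 − p1)/80 + p2(1 − p2)/80], z = 1.96 for 95% and 1.645 for 90%.

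For D = 10: p1 = 0.4375, p2 = 0.3125, SE = √[(0.2461 + 0.2148)/80] = 0.0759. The 95% interval is 0.125 ± 0.149, or -2.4 to +27.4 points. The same formula gives:

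| D | Difference (points) | 95% CI | 90% CI |
| --- | --- | --- | --- |
| 4 | +5.0 | -9.6 to +19.6 | -7.3 to +17.3 |
| 5 | +6.3 | -8.4 to +20.9 | -6.1 to +18.6 |
| 6 | +7.5 | -7.2 to +22.2 | -4.9 to +19.9 |
| 7 | +8.8 | -6.0 to +23.5 | -3.7 to +21.2 |
| 8 | +10.0 | -4.8 to +24.8 | -2.4 to +22.4 |
| 9 | +11.3 | -3.6 to +26.1 | -1.2 to +23.7 |
| 10 | +12.5 | -2.4 to +27.4 | 0.0 to +25.0 |

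All seven rows fall under the no-effect wording. The 95% interval contains 20 points for D = 5 to 10, and the 90% interval for D = 7 to 10. Newcombe intervals give the same picture (D = 10: -2.5 to +26.7).

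**Step 3: stage 1.** With 13/43 placebo cures, D1 = 1 gives +2.3 points (95% CI -17.3 to +21.9; 90% upper limit 18.8). D1 = 0 has a 95% upper limit of 19.4. Only D1 = 1 is affected, and with a 90% interval nothing is.

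**Step 4: other placebo rates.** For placebo rates from 20% to 51%, the lowest affected final D is 4 to 6 with a 95% interval and 6 to 8 with a 90% interval. At stage 1 with a 95% interval, no result is affected at 20%, D1 = 1 at 31%, and D1 = 0 or 1 at 40% to 51%. With a 90% interval, D1 = 1 is affected only at 50% to 51%.

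**Step 5: D = 11.** The Outline and Section 15.3.4 call more than 11 positive and less than 11 negative, so 11 itself is unclassified. Section 11 requires more than 11, which makes 11 a failure. Power at 51% against 31% is 0.805 if 11 counts as success and 0.762 if it does not.

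**The case against.** The case for leaving this alone is that it is only wording. The boundaries, sample size and decision to stop or continue are the same whichever label is used. The English is evidently translated. Section 15.3.4 describes the boundaries as deciding on the null hypothesis, and Section 9.3.2 points to a go/no-go reading. Interval reporting, and its adjustment for two stages, is commonly left to the statistical analysis plan.

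Much of this stands. The boundaries are sound, and the absence of a mandatory adjusted interval is not counted here as a defect. What remains is that three sections agree on a substantive negative conclusion which the test cannot support. An analysis plan that followed the protocol would inherit it.

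A reader might infer more than the documents support:

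- **That the protocol claims proof of no effect.** It speaks of judging and concluding; proof is not its term.
- **That the chance of missing a real benefit measures the defect.** The rule fails in 19.5%, 41% and 67% of trials with true benefits of 20, 15 and 10 points (success at 11 or more). These figures are one minus power. Rewording would not change them, and the first is the planned type II error.
- **That every failure is affected.** At 25/80 placebo cures, D of 4 or less has a 95% upper limit below 20 points, though smaller benefits remain possible.
- **That both stages are equally affected.** Stage 1 rests on D1 = 1 alone.
- **That one more cure after D = 10 reverses the conclusion.** This assumes 11 is a success, which no section states.

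**Conclusion.** The concern holds, mainly for the final analysis. The protocol turns failure of a one-sided 5% superiority rule into a conclusion that PGA has no effect or is not effective, with no margin behind it and at odds with the exploratory purpose in Section 9.3.2.

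Its size is a band of results: final D from 5 to 10 with 95% intervals, or 7 to 10 with the 90% intervals that match the one-sided 5% test, plus D1 = 1 at stage 1 with a 95% interval only. This assumes 80 (or 43) evaluable patients per group, placebo cures near 31%, and fixed-sample Wald intervals that ignore the interim look. It should be corrected, but it does not call the design or its boundaries into question.

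**What to change.** Keep +2 and +11 as the go/no-go rule. In Section 15.3.4, Section 11 and the Outline:

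1. Replace the no-effect and not-effective conclusions with: *superiority of PGA not demonstrated; criterion for further development not met*.
2. Always report the difference in regression rates with a 95% confidence interval that allows for the two-stage design.
3. State that a 20-point effect is excluded only if the upper limit is below 20 points.
4. Reconcile the three sections on D = 11, and quote the power that goes with the rule chosen.

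The cost is protocol wording and one interval, with no extra patients or procedures. The downside is that a failed trial with D of about 5 to 10 can no longer be presented as definitively negative.

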### 15.3.5 Analysis of secondary primary efficacy endpoints

Secondary efficacy variable 1: Reid Colposcopic Index

0-2 Score: Likely to be CIN I

3-4 Score: Overlapping lesion - likely to be CIN I or CIN II

5-8 Score: Likely to be CIN II

The comparison between the baseline scores and the difference of the scores after 12 weeks will be confirmed through the t-test or the Wilcoxon rank sum test. In addition, considering the multinomial distribution of the grading system (0-2, 3-4, 5-8 points), the cumulative or ordinal logistic model of the changes in the grading system after 12 weeks compared to baseline.

Secondary efficacy variable 2: Pap Smear Test

The reading standard is based **on the 2001 Bethesda System for Reporting Cervical Cytologic Diagnoses**. The results of the study were divided into 6 stages: Negative, ASC-US, ASC-H, LSIL, HSIL, and Invasive cancer (Cervical carcinoma). Considering the multinomial distribution, And the cumulative or ordinal logistic model is used to analyze changes in the classification stage 3 months after the baseline.

Secondary efficacy variable 3: HPV DNA Chip Test

The HPV DNA Chip Test is a test to determine the type of virus infection. It is classified as positive or negative according to the test result. GEE (Generalized Estimating Equation) or Generalized Linear Mixed Model is considered to determine time-dependent changes, group-to-group differences, and time-to-group interactions for baseline versus measured clearance.

Secondary efficacy variable 4: HPV HC Ⅱ assay

GEE (Generalized Estimating Equation) or Generalized Linear Mixed Model is considered to determine time-dependent changes, group-to-group differences, and time-to-group interactions for baseline versus measured clearance.

Secondary efficacy variable 5: NK cell activity

To compare the results of NK cell activity measured at 4 weeks, 8 weeks, and 12 weeks versus baseline (0 week), the mean difference between the baseline and 12-week NK cell levels was calculated as t - Black or Wilcoxon rank sum test.

Secondary efficacy variable 6: MHC class II CD8, CD56 population

GEE (Generalized Estimating Equation) or Generalized Linear Mixed Model is considered to determine time-dependent changes, group-to-group differences, and time-to-group interactions for baseline versus measured clearance.

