### 15.1.2 Secondary Validity Variables

Compared to baseline (within -4 weeks) before drug administration Reid Colposcopic Index at 12 weeks after drug administration

Compared to baseline (within -4 weeks) before drug administration Pap smear test results at 12 weeks after drug administration

Comparison of HPV DNA chip test results at 12 weeks after drug administration compared to Baseline (within -4 weeks) before drug administration HPV HC Ⅱ assay results at 12 weeks after drug administration compared to baseline (within -4 weeks)

Comparison of results of NK cell activity at 4, 8 and 12 weeks after drug administration compared to baseline (0 week) before drug administration

(MHC class II) CD8, CD56 population at 4 weeks, 8 weeks, and 12 weeks after administration of drug compared to baseline (0 week) before drug administration.

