###### 15.3 Statistical analysis method

**15.3.1 General principles of analysis**

The purpose of this study was to investigate the effect of oral administration of polygamma glutamic acid (γ-PGA) on the cervical intraepithelial dysplasia (CIN) Phase II clinical studies to confirm. All data obtained in this study are summed up as mean ± standard deviation for continuous data and categorical data for the number of subjects (fraction), and various summary statistics are presented when necessary. If it is necessary to provide an interval estimate, a 95% confidence interval shall be provided.

In the statistical analysis of this data, the first validity criterion, the healing rate, is to be carried out by a one-sided test at a significance level of 5% based on the method of Jung (2008) in the appropriate validity analysis group defined in 15.2. In the analysis other than the primary efficacy evaluation item, the two-sided test is performed at the significance level of 5%. In addition to the efficacy evaluation methods and safety evaluation methods described in 15.3.4 and 15.3.6, when prognostic factors contributing to the outcome variables such as age, perinatal risk, baseline laboratory values, (Eg, logistic model, ANOCOVA, generalized linear model, etc.).

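### CD8/CD56 model: week 0 is not specified as a covariate and no PGA-versus-placebo contrast is made decisive; a free but low-materiality improvement

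*Protocol*

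**What the plan says.** Section 15.1.2 defines the endpoint as "CD8, CD56 population at 4 weeks, 8 weeks, and 12 weeks after administration of drug compared to baseline (0 week) before drug administration". The flow chart has the PBMC sample at visits 2 to 5, that is weeks 0, 4, 8 and 12.

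The only analysis given for it, in 15.3.5 and in item 5 of the Outline's statistical analysis, is a GEE or GLMM that is "considered to determine time-dependent changes, group-to-group differences, and time-to-group interactions", with *clearance* given as the outcome. The same sentence serves variable 3 (HPV DNA chip) and variable 4 (HPV HC II). Section 15.3.1 sets the level: "In the analysis other than the primary efficacy evaluation item, the two-sided test is performed at the significance level of 5" per cent.

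NK cell activity, sampled at the same four visits, is treated differently. Section 15.3.5 singles out one comparison for it: "the mean difference between the baseline and 12-week NK cell levels was calculated as t - Black or Wilcoxon rank sum test".

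Section 15.3.1 also allows, in a sentence damaged in translation, for analyses with prognostic factors. It gives baseline laboratory values as an example of a factor and ANOCOVA as an example of a method. It does not name week-0 CD8 or CD56.

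**The concern.** Three effects are listed with equal standing, and they answer different questions.

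- **Time** describes change over visits, whether or not PGA does anything.
- **Group** is a between-arm comparison, but its meaning depends on the outcome. If all four visits are modelled, it averages in week 0, where randomisation makes the expected difference zero. If change from week 0 is modelled, it does not.
- **Time-by-group** is a between-arm comparison of profiles. With four visits it has 3 degrees of freedom.

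None of these, as specified, uses the week-0 value as a covariate, although it is collected on everyone. Section 11 says the study is meant to identify immunomodulatory effects through immunological parameters, and CD8/CD56 is one of two such endpoints. What is at stake is precision, and a clear reading, for that secondary question.

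The sentence also gives *clearance* as the outcome. That can fit the HPV tests but has no meaning for a cell population.

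**Working it through.** **The plan's own figure.** The protocol states no power for CD8/CD56. Its only size is for histology: "The Sample size is total 160 patients, 80 patients per group when the Single stage method", with "significance level : 0.05, statistical power : 80%, one-sided test". Exact binomial enumeration of the two-stage rule (continue if the difference is at least 2 at 43 per group; success if at least 11 at 80 per group) at 51% versus 31% gives power 0.805, against 0.800 stated. With 20% dropout, 80/(1 − 0.2) = 100. This supports only the use of 80 per group below.

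**Inputs.** From the protocol: n = 80 per group, visits at weeks 0, 4, 8 and 12, two-sided 5%. Assumed, because the protocol gives none: SD 1, true difference 0.4 SD, equal correlation ρ between visits of 0.3, 0.5 or 0.7, complete data, known variance.

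**Formulas for a sustained effect (0 at week 0, then 0.4 at weeks 4, 8 and 12).** For 1-df contrasts, power ≈ Φ(Δ/SE − 1.96).

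- Four-visit group effect: Δ = 0.4 × 3/4 = 0.3; SE² = (2/80)(1 + 3ρ)/4.
- Average change from week 0: Δ = 0.4; SE² = (2/80)(1 − ρ)(4/3).
- Baseline-adjusted average of weeks 4, 8 and 12: Δ = 0.4; SE² = (2/80)[(1 + 2ρ)/3 − ρ²].
- Interaction, 3 df: noncentrality λ = (80/2)/(1 − ρ) × Σ(δⱼ − mean δ)² over the four visits. The sum is 0.09 + 3 × 0.01 = 0.12. The 5% critical value is 7.815.

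**At ρ = 0.5.**

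- Group: SE 0.125, ratio 2.40, power 67%.
- Average change: SE 0.129, ratio 3.10, power 87%.
- Adjusted average: SE 0.102, ratio 3.92, power 97%.
- Interaction: λ = 80 × 0.12 = 9.6, power 74%.

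| Test, sustained 0.4 SD effect | ρ = 0.3 | ρ = 0.5 | ρ = 0.7 |
|---|---|---|---|
| Group effect over four visits | 79% | 67% | 58% |
| Interaction, 3 df | 58% | 74% | 93% |
| Average change from week 0, unadjusted | 74% | 87% | 98% |
| Average of weeks 4–12, adjusted for week 0 | 97% | 97% | 99% |

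**Like for like, without guessing the pattern.** The joint 3-df test of the group differences at weeks 4, 8 and 12, adjusted for week 0, can be set against the 3-df interaction. For a sustained effect it has 91/92/98% against 58/74/93%. For an effect at week 4 only it has 64/77/94% against 58/74/93%. The gain therefore comes from the covariate and not only from choosing a favourable contrast.

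**Single visit, week 12, sustained effect.** Unadjusted change has SE² = (2/80) × 2(1 − ρ) and power 57/72/90%. Adjusted for week 0, SE² = (2/80)(1 − ρ²) and power is 76/83/94%.

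**Time effect.** If both arms rise by 0.3 SD after week 0 and PGA does nothing, the time test rejects with probability 92/98/100%.

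**Using either between-group effect.** With equal correlation, the four-visit group test and the interaction are independent, so a claim on either has null error 1 − 0.95² = 9.75% per population.

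**The case against.** The strongest objection is that naming the deciding contrast of a secondary repeated-measures model is ordinary SAP content. The SAP is not shown, and the protocol says only that a model is considered. This stands: the absence of a named contrast would not by itself be worth raising. What remains is that the protocol does write down a set of effects, and a better model is available from data already collected.

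Several stronger readings are tempting and are not supported.

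- *Three rival treatment tests.* There are two. The time effect is not a PGA-versus-placebo comparison, and the group effect is one in plain words.
- *Opposite conclusions.* The two can differ on significance, not in direction on this evidence. At ρ = 0.5 with a sustained effect they would disagree in about 0.67 × 0.26 + 0.74 × 0.33 = 42% of trials.
- *Always very different power.* For an effect building linearly to 0.4 SD at week 12, both have 45% at ρ = 0.3.
- *The group effect is always diluted.* Only if week 0 is an outcome. The wording of 15.1.2 makes change from baseline at least as natural. On that reading the group effect has 74/87/98% for a sustained effect.
- *Baseline adjustment is excluded.* It is not; 15.3.1 leaves room for it without specifying it here.
- *Naming one contrast always gains power.* At ρ = 0.5, the adjusted average has 26% against 74% for the interaction if the effect is at week 4 only. The adjusted week-4 contrast has 16% against 60% if the effect builds to week 12, and 5% against 74% if it appears only at week 12.

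Materiality is also low. Section 6 gives the regression rate as the objective, 15.3.4 decides efficacy on histology, and 9.3.2 calls the study exploratory.

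**Conclusion.** The point holds in a limited form. As worded, the CD8/CD56 analysis does not specify the week-0 covariate, includes an effect (time) that cannot show efficacy, and borrows an outcome term that does not fit. Adjusting for week 0 improves power over the matching unadjusted test in each comparison above: for the week 4–12 average, from 74/87/98% to 97% or more with a sustained effect; for the 3-df tests, from 58/74/93% to 91/92/98%.

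These figures rest on an assumed 0.4 SD difference, correlations of 0.3 to 0.7 equal between all visits, and 80 complete patients per group. Other values would change the size of the gain.

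A reader might infer that the immune results are uninterpretable or that the trial's conclusion is at risk. The documents do not support that. No stopping rule, sample size or efficacy decision depends on CD8/CD56. This is an improvement to consider, not a necessary correction.

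**What to change.** In 15.3.5 and the Outline, for variable 6:

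1. Model the week 4, 8 and 12 values with the week-0 value as covariate, plus visit, group and visit-by-group terms.
2. Before unblinding, make one PGA-minus-placebo contrast decisive for each population, and report the other visits as supportive. Week 12 would match the NK activity analysis. The average over weeks 4 to 12 or another single visit is equally open; the choice is the sponsor's.
3. State that the time effect is descriptive and not evidence of efficacy.
4. Replace *clearance* with the CD8 or CD56 population value.

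Variables 3 and 4 carry the same list of effects, so their wording should be checked at the same time. They are measured only at visits 1 and 5, so the visit structure in step 1 does not carry over to them.

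The cost is wording in the protocol and SAP, with no extra visits or samples. The real price is commitment: a contrast that misses the true pattern of effect loses power, as shown above.
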